## Abstract

**Background:**

Retrospective and descriptive molecular epidemiology studies have shown that *Mycobacterium tuberculosis* whole genome sequencing can identify outbreaks and disease transmission events with higher resolution than conventional epidemiological investigations. Those studies have strengthened our understanding of genomic polymorphisms correlating with person-to-person transmission and helped resolve putative transmission clusters. To date, systematic genomic surveillance programs implemented for *M. tuberculosis* were only implemented in low-incidence settings. The purpose of this study is to determine whether there is an impact of routine *M. tuberculosis* whole genome sequencing on tuberculosis case detection in a high-incidence setting.

**Methods:**

A cluster randomized controlled trial will be performed. Forty-eight rural village groups (or Fokontany) in the Vohibato district of Madagascar will be randomized to one of three interventions arms. Arm 1 (standard of care) involves healthcare facility-based passive case detection with smear microscopy testing. Arm 2 (best practice) consists of active case finding and Xpert MTB/RIF Ultra PCR testing followed by household contact investigations. Arm 3 (novel intervention) includes the same interventions as arm 2, with addition of sputum culture and *M. tuberculosis* whole genome sequencing for all newly diagnosed cases. In arm 3, molecular suggested putative outbreaks are investigated, and additional TB suspects are appropriately tested. The intervention observational period will be 2 years. The primary outcome will be the number of detected cases/100,000/year in each arm after 1 year of intervention.

**Discussion:**

This study is designed to determine whether there is an impact of prospective whole genome sequencing-based molecular typing on tuberculosis case detection in high-incidence settings. Investigating potential outbreaks and focusing active case finding in spatiotemporal settings where disease transmission is suggested by genomic typing is hypothesized to improve case detection in rural communities.

**Trial registration:**

ClinicalTrials.gov NCT05406453. Retrospectively registered on June 6, 2022.

**Supplementary Information:**

The online version contains supplementary material available at 10.1186/s13063-024-08537-4.

## Introduction

### Background and rationale {6a}

Conventional tuberculosis (TB) control interventions are predicted to fail in meeting the World Health Organization (WHO) End TB Strategy objective of eliminating TB by 2035 and the WHO calls for discovery, development, and rapid uptake of new tools and interventions [1, 2]. *Mycobacterium tuberculosis* whole genome sequencing (WGS) can detect both TB person-to-person transmission and TB drug resistance from the same clinical sample using the same diagnostic platform [3, 4]. Its use for drug susceptibility testing (DST) is driving its implementation in many countries with international TB genomics consortia support and WHO technical guidance [5–7]. *M. tuberculosis* WGS can also uncover unsuspected chains of transmission and support epidemiologic investigations beyond the usual contact tracing that is already recommended by WHO [8]. The principle behind WGS-based inference of TB transmission is that mutations, or single nucleotide polymorphisms (SNP), occur in the bacterium over time; if two isolates are very related or divergent (below or above the number of SNPs expected for a given period of time), transmission may respectively be suggested or refuted [9]. Retrospective and descriptive molecular epidemiology studies have shown that *M. tuberculosis* WGS can identify person-to-person transmission events with higher resolution than previous molecular typing methods [10]. To date, no data has showed that prospective and systematic sequencing favorably impacts TB case detection or limits the spread of disease. The hypothesis that prospective recognition of transmission events could lead to diagnosis and treatment of additional patients and further limit transmission remains to be proven. TB transmission is impacted by community social, spatial, and cultural dynamics [11]. In high-incidence settings, TB control strategies are designed and implemented through programmatic planning by public health authorities. In this context, a cluster randomized control trial study design comparing different intervention bundle strategies in distinct but comparable communities is well adapted to assessing the value of prospective TB molecular epidemiology for disease control within communities.

Madagascar exemplifies the challenges of TB control in remote and low-resource settings as the country only diagnoses 61% of its cases [12]. Access to TB diagnosis was shown to represent the most important gap in the Malagasy TB care cascade [13]. On the other hand, incidence of HIV and multi-drug resistant tuberculosis (MDR-TB) are low and the majority of the population is rural, isolated, and geographically stable [13, 14]. These conditions offer a unique opportunity to achieve substantial progress towards TB elimination if case detection is significantly improved and transmission interrupted. The country’s National Tuberculosis Program reference laboratory at the Institut Pasteur de Madagascar has recently implemented TB WGS-based diagnostics as a research use only assay for surveillance and DST [15]. Madagascar is hence a well-adapted setting to assess the impact of molecular typing on disease control in high-incidence settings.

## Objectives {7}

The study objective is to measure whether there is an impact of systematic and prospective *M. tuberculosis* WGS on TB case detection in high-incidence settings. We hypothesize that WGS-guided epidemiologic investigations improve case detection by adapting contact tracing strategies to local transmission patterns.

## Trial design {8}

This factorial, three-arm, open cluster randomized controlled trial (cRCT) will compare three TB control interventions in the Vohibato rural district of Madagascar. In rural Madagascar, villages of ~200 people include ~20 households and are administratively grouped in Fokontany (smallest administrative unit), of ~9 geographically close villages”. Fokontany (“1800 inhabitants”) will be the unit of randomization and analysis for this trial. Fokontany satisfying inclusion/exclusion criteria (eligibility criteria) will be selected and 48 out of them will be randomized by minimization to three equal arms [16].

## Methods: participants, interventions, and outcomes

### Study setting {9}

The study will take place in Vohibato district located in the Haute Matsiatra region in Madagascar. The district of Vohibato includes 232,518 inhabitants and is subdivided in 14 communes and 145 Fokontany [17]. Field case finding and patient recruitment activities will be deployed in rural Fokontany (i.e., Malagasy administrative entity consisting of an aggregation of villages). Local public TB CDT will perform primary diagnostic assays. The National Tuberculosis Program (NTP) reference laboratory hosted at the Institut Pasteur de Madagascar (IPM) will perform reference testing including bacterial culture and sequencing.

### Eligibility criteria {10}

There are 145 Fokontany in Vohibato. Of those, 132 were categorized as rural in this study because of their location associated with limited access to healthcare facilities and urban areas. Those 132 Fokontany correspond to the target study population. Fokontany with at least one active TB case confirmed during the 6-month period prior to randomization will be eligible. Fokontany further than 100 km from a primary care TB clinic or that elicit safety concerns or geographic accessibility issues will not be included. There are 56 Fokontany which fulfill those eligibility criteria. Out of those, 48 will be allocated in three equal arms using randomization by minimization (see “ Assignment of interventions: allocation” section).

### Who will take informed consent? {26a}

Since TB screening and laboratory testing of symptomatic patients are recommended as per NTP guidelines and represent the standard of care, the need for informed consent will be waived for inhabitants of Fokontany randomized to arm 1. Written informed consent will only be obtained upon confirmation of a TB diagnosis for patients living in Fokontany randomized to arm 2 and arm 3, prior to conducting sputum culture for genomic DNA sequencing and outbreak investigation which are not part of standard of care. Clinical research personnel with up-to-date training in good clinical practices (GCP) will obtain participants informed written consent before inclusion. The study consent form will be available to participants in French and Malagasy and is available as Supplementary Materials 2. The consenting process will follow local ethics guidelines from the local ethics board. Should patients refuse to participate in the study, they will still have access to the same standard of care, as per local NTP guidelines. Participants will be able to withdraw from the study and request that their data be deleted at any time. Amendments to the study protocol will be required and re-consenting will be required for collection and use of additional participant data or biological specimens.

### Additional consent provisions for collection and use of participant data and biological specimens {26b}

N/a: We will not conduct any ancillary studies.

## Interventions

### Explanation for the choice of comparators {6b}

Arm 1 “standard of care” will provide a country contextualized baseline for TB diagnosis and notifications which reflects the current NTP strategy. Arm 2 “best practice” will provide a measure of how well current recommendations including WHO guidance perform against the study intervention in the specific study context. Data from arm 2 will also allow to assess whether perceived added value of WGS is driven by the impact of diagnostic (Xpert MTB/RIF Ultra PCR) sensitivity or active rather than passive case finding.

### Intervention description {11a}

Case finding strategies are either passive—meaning health facility-based and limited to self-presenting patients—or active—meaning health system-initiated and targeting patients beyond healthcare infrastructures. TB diagnosis either relies on smear microscopy (sensitivity 63%) or polymerase chain reaction (PCR) molecular testing (sensitivity 89%) [18–21]. Contact tracing activities prioritize high-risk household contacts [9]. Clusters will be randomized into one of 3 arms, all integrating a bundle of case finding, laboratory diagnosis, and contact tracing strategies (see Fig. 1). Arm 1 will represent the high-burden low- and middle-income countries (LMIC) “standard of care” and include passive case finding, smear microscopy, and household contact tracing. Arm 2 will represent WHO recommended “best practice” and additionally include Xpert PCR MTB/RIF Ultra and active case finding in which clinical teams will visit Fokontany to seek out and test individuals presenting TB-compatible symptoms. Arm 3 will represent the “novel intervention” which, in addition to interventions included in arm 2, will add sputum culture, *M. tuberculosis* WGS and epidemiologic investigations to detect additional TB cases. *M. tuberculosis* WGS will be performed using already implemented Oxford Nanopore Technologies™ [15]. The offline or cloud-based TB bioinformatic analysis pipeline TB Pore Cluster will be used for isolates clustering and transmission detection. SNP transmission thresholds (5–12 SNPs) were previously reported from low-incidence countries [22]. To avoid the overlook of transmission events and maximize TB detection, a minimally stringent threshold (12 SNPs) will be used to trigger field epidemiologic investigations. When molecular typing suggests patients clustering, field clinical teams will investigate epidemiologic correlates of transmission events such as co-farming and co-attendance to school or service institutions. If such are present, additional contact tracing and testing based on newly identified epidemiologic denominators between related patients will be performed.

**Fig. 1 Fig1:**
[figure not shown]
cRCT study arms, sample size, anticipated outcomes, and intervention strategies

### Criteria for discontinuing or modifying allocated interventions {11b}

Interventions will be implemented at healthcare system level. No compliance issues or loss to follow-up of clusters are anticipated. No modification to the allocation or interventions in included Fokontany is planned regardless of the interim analyses study results.

### Strategies to improve adherence to interventions {11c}

To ensure high rates of initial consent and retention in the study during local investigation, consultation with, and consenting from, community leaders and health officials will be sought. Comprehensive study information will also be provided in Malagasy to participants.

### Relevant concomitant care permitted or prohibited during the trial {11d}

No TB-related non-governmental organization or novel country-initiated interventions are planned in the study area.

### Provisions for post-trial care {30}

All TB patients will be referred to NTP for free access treatment and clinical follow-up. This study involves no risk for the safety of participants.

### Outcomes {12}

Globally, TB incidence is reported as number of cases/100,000 population/year. TB cases are defined by WHO as pulmonary or extra-pulmonary TB, adult or pediatric TB, and bacteriologically confirmed or non-confirmed TB. Within underdeveloped health systems, number of cases diagnosed by NTPs (case detection/100,000/year) is usually less than real incidence as estimated by WHO. Case detection/100,000/year is a standardized WHO indicator allowing comparisons between interventions. It is also the best available surrogate marker for impact on transmission and short- and long-term disease control. In this study alike, the primary outcome will be the difference in TB incidence (TB case detection/100,000/year) between arms 3 and 2 during the first year of the study intervention. Secondary outcomes will include the difference in TB incidence between arms 3 and 1 and between arms 2 and 1. Secondary outcomes will also include all the above incidence difference between arms during 2 years of intervention. For all primary and secondary outcomes, sub-group analyses based on biological sex, age, and baseline cluster characteristics will also be performed. Generally, an increase in TB detection is desirable since additionally diagnosed patients would otherwise go unnoticed, transmit, and either self-present to care at a later stage of disease or die. In this study, the objective will not be to accurately assess disease incidence but rather to measure the increase in the primary outcome between arms.

### Participant timeline {13}

Active case finding and associated laboratory testing will be performed every year in arms 2 and 3 clusters. Study interventions and data capture will last 2 years for all clusters.

### Sample size {14}

This study will be powered to demonstrate superiority of arm 3 “novel intervention” over arm 2 “best practice” after 1 year. Given the purely incremental nature of arm 3 “novel intervention,” it is assumed it cannot be inferior. Using (i) realistic anticipated outcomes described below with 116% increase in TB case detection rate from 95/100,000/year to 206/100,000/year, (ii) Fokontany as the analysis unit, (iii) intraclass correlation coefficient (ICC) of 0.0005 for sample size adjustment, (iv) average Fokontany cluster size of 1800 inhabitants, and (v) assuming a one-sided *α* = 0.05 test with 80% power, we estimate the number of Fokontany in each arms should be 16 to allow detection of the TB detection rate difference using a simple *t*-test weighed by Fokontany size [23]. TB incidence data from every Fokontany in the Haute Matsiatra region were used to perform sample size calculation. Given the sufficient number of eligible Fokontany in the Vohibato district, 48 Fokontany from this district will be selected to increase feasibility and cluster homogeneity. Multiple simulations were performed to strengthen this sampling size strategy and are presented as Supplementary Materials 1. To estimate anticipated outcomes in each arm, to calculate the ICC and calculate sample size, we used (i) Madagascar TB incidence estimates from WHO, (ii) NTP data disaggregated by primary healthcare facility where services are similar to study interventions, (iii) a comprehensive and systematic baseline survey, and (iv) pilot studies assessing clusters interconnections and impact of arm 1 and arm 2 interventions (see Fig. 2) [11]. Using demographic, distance to healthcare facility, and baseline TB detection rates, the ICC was calculated to be 0.0005. This suggests homogeneity between clusters, which agrees with findings of social network studies performed in the same area and ICC values used in sub-Saharan African studies measuring TB case finding strategies in similar contexts [24]. For arm 1 “standard of care,” anticipated outcomes are adjusted to most reliable, contextualized, and comprehensive primary data from the baseline survey, 75/100,000/year. Using all four sources of preliminary data, we determined realistic anticipated outcomes for arm 2 to be 95/100,000/year and 206/100,000/year for arm 3 [11, 12, 14].

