## Statistical methods

### Statistical methods for primary and secondary outcomes {20a}

First, we will calculate TB case notification rates for each Fokontany. The overlapping TB cases resulting from our RCT study and from NTP report will be counted once in the outcome measures. The primary analysis will compare notification rates between arms after 1 year, using a simple *t*-test and nonparametric Mann–Whitney *U* test weighed by Fokontany size with Fokontany as the unit of analysis. Detection rate differences and 95% confidence intervals (CI) will be reported. The ICC will be calculated from the output of one-way analysis of variance (ANOVA) [27]. As a secondary analysis, the longer-term effect of sustained interventions will be evaluated for 2 years. The longitudinal impact of interventions will be evaluated with a linear mixed-effects model weighed by Fokontany size again conducted at the cluster level. The model will include the yearly TB detection rate, the study arm (1, 2, and 3), the year (first and second), and the interaction arm × year as the fixed effects and Fokontany as the random effect. The least squares mean estimates with 95%CI will be computed from the models. The longitudinal pattern of TB detection rate for each study arm and for each Fokontany will be presented graphically by 6- and 12-month interval. To estimate Fokontany size, we will use two approaches. First, we will consider primary data from the 2019 INSTAT-World Bank census (pilot study) with the 2.7% World Bank estimated annual increase [28, 29]. Then, we will consider the population reported by health authorities upon case finding visits. R software will be used for analyses.

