### Interim analyses {21b}

Interim results will be analyzed every 12 months by the steering committee. If a statistically significant benefit is shown early in the study, results will be disseminated, and the study will be continued until interventions have been implemented for a 2-year period in all clusters to assess longer term impact on TB control (statistical methods for primary and secondary outcomes). If no significant difference between groups is seen after 1 year, this study will be considered negative. We will complete 2 years of intervention to further investigate transmission risk factors emerging from outbreak investigations and long-term impact on case detection rates.

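### The 80% power reproduces, but the cluster size of 1,800 and the arm 2 rate of 95 do not fit other figures in the protocol, and a non-significant first year would be called negative at low power for smaller gains

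*Protocol article*

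**What the plan says.** The Sample size section takes a "116% increase in TB case detection rate from 95/100,000/year to 206/100,000/year", an intraclass correlation of 0.0005, an "average Fokontany cluster size of 1800 inhabitants" and a one-sided 5% test with 80% power. It arrives at 16 Fokontany per arm for a t-test weighted by Fokontany size. Arm 1 is expected to detect 75 per 100,000 per year.

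Other sections bear on these inputs:

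- **Trial design** supports 1,800: "villages of ~200 people include ~20 households and are administratively grouped in Fokontany (smallest administrative unit), of ~9 geographically close villages".
- **Study setting** points lower: "The district of Vohibato includes 232,518 inhabitants and is subdivided in 14 communes and 145 Fokontany".
- **Eligibility criteria** counts 132 of the 145 Fokontany as rural and 56 as eligible.
- **Intervention description** gives a sensitivity of 63% for smear microscopy and 89% for PCR. Arm 2 adds PCR and active case finding to what arm 1 does.
- **Interim analyses** fixes the reading of the first-year result: "If no significant difference between groups is seen after 1 year, this study will be considered negative".

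**The concern.** Power is only as good as its inputs, and two of them can be checked against the protocol itself. The cluster size is larger than the district totals allow on average. The arm 2 rate is lower than the better test alone could produce, although arm 2 also includes active case finding. Both discrepancies flatter the design: larger clusters add information, and a low arm 2 rate widens the primary contrast of arm 3 against arm 2.

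At stake is how a non-significant first year will be read. The protocol commits in advance to calling it negative. If the design can reliably detect only a rise of about the assumed size, that label would turn an inconclusive result into a statement that sequencing-guided investigation does not help.

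**Working it through.** **1. Reproducing the plan.** Let p1 = 0.00095, p2 = 0.00206, p̄ = 0.001505, one-sided α = 0.05 and power 80%.

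Persons per arm before clustering: n = [1.645·√(2p̄(1−p̄)) + 0.842·√(p1(1−p1) + p2(1−p2))]² / (p2−p1)² = 15,081.

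Design effect: 1 + (1,800−1)×0.0005 = 1.8995.

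Clusters: 15,081×1.8995/1,800 = 15.9, rounded up to 16.

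Power with 16 clusters (effective n = 16×1,800/1.8995 = 15,162 per arm):

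- normal approximation: 80.2%
- noncentral t with 30 degrees of freedom: 78.6%
- beta-binomial simulation of the size-weighted t-test: 80.4%

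The printed result follows from the printed inputs. Ranges below give the t and normal figures.

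**2. Cluster size.** 232,518/145 = 1,604. At 1,800 each, the 132 rural Fokontany would hold 132×1,800 = 237,600 people, which is 5,082 more than the whole district.

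At 1,604 the design effect is 1 + 1,602.6×0.0005 = 1.801, and the requirement is 15,081×1.801/1,603.6 = 16.9, so 17 clusters (18 with the t reference). Power with 16 is 76.3% (t) to 78.0% (normal).

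**3. Arm 2 rate.** If every arm 1 case is diagnosed by smear, replacing smear by PCR gives 75×89/63 = 106. If only a share s of cases scales with test sensitivity, 95 is reached from the test alone when s = (95/75 − 1)/(89/63 − 1) = 0.267/0.413 = 0.65. So 95 leaves room for a gain from active case finding only if fewer than about 65% of arm 1 cases are smear-diagnosed.

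Power with 16 clusters per arm and arm 3 at 206 (t / normal):

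| Arm 2 rate | Size 1,800 | Size 1,604 |
|---|---|---|
| 95 | 78.6% / 80.2% | 76.3% / 78.0% |
| 106 | 69.5% / 71.3% | 67.2% / 68.9% |
| 120 | 56.7% / 58.4% | 54.5% / 56.1% |
| 140 | 38.5% / 39.7% | 36.9% / 38.0% |

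**4. Smaller effects, keeping the plan's own 95 and 1,800.** A 50% increase (95 to 142.5) has 32-33% power, and 95 to 150 has 38-39%. For scale, one arm holds 16×1,800 = 28,800 people, so the planned rates mean 28,800×0.00095 = 27 cases against 28,800×0.00206 = 59. The design is sized for a gain of about 32 cases on a base of 27.

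**The case against.** **On cluster size.** The figure 1,604 is a district mean of undated population and includes 13 non-rural Fokontany. Trial design independently supports 1,800, and the calculation used data from the whole Haute Matsiatra region. The analysis section projects population from the "2019 INSTAT-World Bank census (pilot study) with the 2.7% World Bank estimated annual increase". If 232,518 were a 2019 count, 1,604 would become 1,737 after three years (about 79.5% power, normal approximation) and 1,784 after four. Requiring a recent case also favours larger Fokontany. All of this stands: it may explain part or all of the gap, but the protocol does not say which explanation applies.

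**On arm 2.** Multiplying by 89/63 assumes that all notified cases scale with test sensitivity. The Outcomes section also counts extra-pulmonary and bacteriologically unconfirmed disease, which need not. The rates drew on pilot studies of the arm 1 and arm 2 interventions, and Fig. 2 and Supplementary Materials 1 were not available for this review. This too stands, so 106 is an upper figure for the test effect under a stated assumption, not a corrected arm 2 rate.

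**On the negative label.** It does not change conduct, because the trial runs two years regardless, and the wording would be open to question even at exactly 80% power. That is true. But the rule is fixed in advance, and low power for smaller gains follows from the plan's own 95 and 1,800.

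**Stronger readings that the document does not support:**

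- A reader might infer that clusters were assumed equal and that unequal sizes cut power to 71-76%. No section says sizes are equal, and no coefficient of variation is given. At an assumed coefficient of 0.5 the design-effect formula gives 76.2%, but simulation of the weighted test gives 79.1%.
- A reader might infer from "the country only diagnoses 61% of its cases" that 75/0.61 = 123 caps arm 3. That applies a national share to a local rate. A true incidence of 206 needs only 75/206 = 36% local detection, and a first active round can find prevalent cases.

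**Conclusion.** The concern holds in a limited form. The 80% is not an arithmetic error, since the inputs as printed give 16 clusters per arm. Two of those inputs need reconciling with the rest of the protocol.

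The cluster-size discrepancy is small, about 2 points of power, and may have an innocent explanation. The arm 2 rate matters more: about 9 points if arm 2 reaches 106, and far more at 120 or 140. That part depends on the share of arm 1 cases diagnosed by smear, which the protocol does not give, and the higher arm 2 rates are sensitivity values, not predictions.

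The conclusion about the negative rule rests on neither input. At the plan's own 95 and 1,800, a 50% gain in detection would miss significance about two times in three and would then be labelled as no benefit.

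**What to change.** - **Sample size:** recompute and restate power from the actual sizes of the selected Fokontany by simulating the planned size-weighted t-test, reporting whatever figure results. Sizes should be at hand, since population is split at the median of the eligible Fokontany for minimization.
- **Sample size and Study setting:** reconcile 1,800 with 232,518/145, stating the year and the set of Fokontany behind each figure.
- **Sample size and Intervention description:** explain how 95 follows from 75 given the two sensitivities and active case finding, including the share of cases diagnosed by smear. Add a table of power for arm 2 rates from 95 to 140.
- **Interim analyses:** replace the negative label with a reading of the 95% confidence interval that the analysis section already plans. A non-significant first-year result is inconclusive unless the upper limit for arm 3 minus arm 2 excludes a worthwhile difference stated in advance.

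The cost is recalculation, one table and some wording. The stated power may become less favourable. No clusters are added and the interventions do not change.
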